## Abstract

**Background:**

Infant HIV diagnosis by HIV DNA polymerase chain reaction (PCR) testing at the standard 6 weeks of age is often late to mitigate the mortality peak that occurs in HIV positive infants’ first 2–3 months of life. Kenya recently revised their early infant diagnosis (EID) guidelines to include HIV DNA PCR testing at birth (pilot only), 6 weeks, 6 months, and 12 months postnatal and a final 18-month antibody test. The World Health Organization (WHO) approved point-of-care (POC) diagnostic platforms for infant HIV testing in resource-limited countries that could simplify logistics and expedite infant diagnosis. Sustainable scale-up and optimal utility in Kenya and other high-prevalence countries depend on robust implementation studies in diverse clinical settings.

**Methods:**

We will pilot the implementation of birth testing by HIV DNA PCR, as well as two POC testing systems (Xpert HIV-1 Qual [Xpert] and Alere q HIV-1/2 Detect [Alere q]), on specimens collected from Kenyan infants at birth (0 to 2 weeks) and 6 weeks (4 to < 24 weeks) postnatal. The formative phase will inform optimal implementation of birth testing and two POC testing technologies. Qualitative interviews with stakeholders (providers, parents of HIV-exposed infants, and community members) will assess attitudes, barriers, and recommendations to optimize implementation at their respective sites. A non-blinded pilot study at four Kenyan hospitals (*n* = 2 Xpert, *n* = 2 Alere q platforms) will evaluate infant HIV POC testing compared with standard of care HIV DNA PCR testing in both the birth and 6-week windows. Objectives of the pilot are to assess uptake, efficiency, quality, implementation variables, user experiences of birth testing with both POC testing systems or with HIV DNA PCR, and costs.

**Discussion:**

This study will generate data on the clinical impact and feasibility of adding HIV testing at birth utilizing POC and traditional PCR HIV testing strategies in resource-limited settings. Data from this pilot will inform the optimal implementation of Kenya’s birth testing guidelines and of POC testing systems for the improvement of EID outcomes.

**Trial registration:**

ClinicalTrials.gov, NCT03435887. Registered 26 February 2018.

**Electronic supplementary material:**

The online version of this article (10.1186/s40814-019-0402-0) contains supplementary material, which is available to authorized users.

## Background

In 2015, an estimated 110,000 new pediatric human immunodeficiency virus (HIV) infections occurred in the 21 Global Plan priority countries [1]. Infant survival and the success of antiretroviral therapy (ART) treatment of HIV-positive infants are associated with early infant age at initiation [2]; thus, early HIV testing, diagnosis, and prompt ART initiation are crucial. In 2015, an estimated 6600 children were infected with HIV in Kenya, a 55% decrease since 2009, but the country’s rate of HIV-exposed infants receiving a routine HIV DNA polymerase chain reaction (PCR) test by 2 months of age has stagnated near 50% since 2011 [3, 4].

One barrier to successful early infant diagnosis (EID) is the waiting time for test results. The sequence of EID services involves multiple time-sensitive steps requiring coordination between medical provider, diagnostic laboratory, and mother/caregiver (“mother”). The standard EID algorithm in Kenya includes mother acceptance of infant testing; specimen collection, transport, and laboratory analysis; communication of results to healthcare providers and caregivers; and linkage to care, including opportunistic infection prophylaxis for all HIV-exposed infants and ART for HIV-positive infants [5]. All steps are susceptible to delays and patient loss to follow-up [5–7]. Traveling long distances for clinical care adds logistical and resource barriers to successful HIV treatment [8].

Innovative strategies with potential to accelerate the delivery of appropriate care to HIV-exposed infants include launching EID at birth rather than the standard 6 weeks of age and streamlining the EID cascade [9]. While these approaches are promising, resource constraints for all stakeholders in EID services (e.g., providers, laboratories, and mothers) require consideration. Adding a testing time point at or near birth, with standard-of-care (SOC) or point-of-care (POC) technology, would likely require more clinical and laboratory workload and equipment capacity [10], and potentially more travel to the clinic by mothers and infants. Conventional testing of HIV-exposed infants has not been initiated until 6 weeks of age because DNA PCR test sensitivity is lower in newborns and neonates (68% and 88% at birth and 4 weeks [11]), intrapartum (IP) HIV infections are not detectable immediately after birth, and the 6-week time point coincides with immunization visits. HIV-infected infants first tested around 6 weeks often are initiated on ART at median ages of 16.0 to 24.5 weeks [12–15], which is too late to mitigate the early peak in mortality around 8–12 weeks of age [16]. In Kenya, 61% of pregnant women deliver in a health care facility and 20% of the infants delivered at home receive a postnatal checkup within 1 week of birth [17]; therefore, testing performed at birth or first clinical contact could accelerate ART initiation in HIV intrauterine-infected infants. Recent recommendations by the WHO and the Kenya Ministry of Health [18, 19] reflect a consensus that birth HIV testing could improve outcomes for HIV-infected infants, even with lower test sensitivity on newborn samples [20, 21]. Kenya’s guidelines call for piloting birth HIV DNA PCR testing of HIV-exposed infants, in addition to further HIV DNA PCR tests at 6 weeks, 6 months, and 12 months. However, pilot data for birth testing (0–2 weeks) is needed prior to national rollout.

In 2016, the WHO prequalified two point-of-care (POC) diagnostic tests for detection of HIV RNA in whole blood samples (Xpert HIV-1 Qual for GeneXpert instruments, manufactured by Cepheid AB; Alere q HIV-1/2 Detect manufactured by Abbott). Both tests are cartridge-based, real-time reverse transcription PCR qualitative assays performed with benchtop instruments that are suitable for operation in the clinic setting and do not require extensive technical training [22, 23]. The initial published evaluations of the Xpert HIV-1 Qual or Alere q HIV-1/2 tests performance were conducted by diagnosticians in the laboratory setting [22–25], showing good sensitivity (93.3–98.7%) and specificity (100%) with infant samples. By definition, the POC test systems provide optimum value in expediting EID if they are performed in the clinic setting, by clinical personnel. Field studies of both the Xpert HIV-1 Qual [26, 27] and Alere q HIV-1/2 [27–29] were performed in clinical care facilities, by medical caregivers. Sensitivity and specificity values were similar to those reported from the laboratory-based qualification studies, but in some instances the field studies produced higher rates of test error [26, 29]. Recent studies with large numbers of HIV-positive newborn infants show close concordance between SOC tests and both of these POC technologies [26, 27]. While analytic performance profiles of these POC technologies have been characterized in field studies, sustainable scale-up and optimal utility in Kenya and other resource-constrained countries requires robust implementation studies in diverse clinical settings. Currently, there is a lack of data to guide strategic implementation of the birth testing timepoint or the Xpert and Alere q POC testing platforms in Kenya. Here, we report the protocol for a pilot study to assess feasibility and preliminary impact of introducing birth testing as an addition to EID services, and to evaluate the two POC platforms in parallel with laboratory-based HIV DNA PCR.

### Objectives

Assess acceptability and uptake of birth testing and both prequalified POC testing platforms in Kenyan clinical settings.Collect pilot data quantifying the efficiency and completeness of EID services augmented with birth and POC testing.Capture pilot data tracking the reliability/performance of both POC platforms for EID services.Engage EID providers in interviews to assess user satisfaction with birth and POC testing and gather feedback on implementation barriers and facilitators.Compute costs of implementing POC testing platforms to fulfill Kenyan EID guidelines.

## Methods

### Study design

In this feasibility study, the new birth EID testing timepoint and two POC infant diagnostic platforms will be implemented on a pilot scale in Kenya. Xpert and Alere q HIV POC platforms will be introduced at four Kenyan government hospitals, for birth and 6-week testing time points. This 18-month study was initiated as a supplement to a parent study (R01HD076673) implementing and evaluating the HIV infant tracking system (HITSystem) [30]. The four hospitals designated as study sites are government hospitals with medium to high patient volume, and geographic variation: two in Kisumu County, one in Nakuru County, and one in Mombasa County. Estimated rates of mother to child transmission of HIV in these three counties in 2015 were 20%, 5%, and 18%, respectively [31]. Phase 1 is a 6-month formative phase in which we will conduct qualitative interviews with parents, providers, and community members to assess stakeholder attitudes toward birth and POC testing and barriers to acceptance or uptake. Feedback will be used to refine operational plans with regard to feasibility and acceptability. Phase 2 is a 12-month feasibility pilot of the two new POC testing strategies. The 12-month implementation period allows time for providers to adopt the new practices and to monitor any fluctuations in uptake or acceptability during this extended period. POC HIV testing will be conducted in parallel with standard laboratory-based HIV DNA PCR, targeting sample collection at birth (0 to 2 weeks) and at 6 weeks (4 to < 24 weeks).

### Phase 1: formative research

Phase 1 seeks to gain information from key stakeholders that will guide operational planning to optimize uptake, acceptability, and feasibility of services at each study site. Approximately *n* = 25 formative interviews with parents, providers, and community members will be conducted at each site; 100 interviews total. Interviews with parents (HIV-positive mothers with prior EID experience and their male partners if available and mother has already disclosed HIV status, *n* = 10 per site) will focus on the impact for the infant and family (confidentiality/disclosure, acceptability of timing of testing and results, and partner support). Interviews with providers who would be involved with POC testing at each site (PMTCT, maternity, and maternal and child health (MCH) nurses; mentor mothers; laboratory technicians; and ART clinicians; approximately *n* = 5 per site) will highlight issues of training, site-specific logistics, patient preparation and counseling, and personnel and resource considerations for implementation. We will also conduct interviews with community members (community health workers, traditional birth attendants, and respected community and religious leaders; approximately *n* = 10 per site) in one rural community within the catchment area of each hospital to elicit attitudes and suggestions regarding the potential for periodic POC HIV testing in hard to access communities. Informed consent will be obtained prior to conducting the interviews in a private setting. Participants will receive 500 Kenyan Shillings (approximately USD $5.00) to compensate for travel and time.

#### Analysis

Interviews will be audio recorded for subsequent transcription, translation, coding, and analysis. Transcripts will be coded independently by two study team members to identify a priori and emergent themes. Discrepancies in coding will be resolved by group consensus. We will develop a codebook with typical exemplars for each theme, noting the frequency and distribution of themes within the larger topic areas. The study team will review themes to inform the POC pilot (phase 2).

### Phase 2: intervention

#### Study design

We will pilot the implementation of POC and birth testing at four government hospitals over a 12 month period. The four study sites will be randomized, using a random number generator, to pilot one of the two POC systems (Xpert HIV-1 Qual for HIV RNA or Alere q HIV-1/2 Detect). SOC diagnostic testing (HIV DNA PCR test on DBS samples) will be conducted in parallel at all study sites, including the newly introduced birth testing time point. Patient flow in the pilot is diagrammed in Fig. 1.

**Fig. 1 Fig1:**
[figure not shown]
Patient flow during evaluation of infant HIV testing strategies. The study will track engagement of enrolled mother-infant pairs in point-of-care (POC) and standard of care HIV DNA polymerase chain reaction (PCR) test technologies through the birth and 6-week testing windows

#### Participant recruitment, eligibility, and consent

HIV-positive pregnant women or mothers of HIV-exposed infants engaged in care at study hospitals will be invited to participate in the pilot. Women can be enrolled either through PMTCT, during pregnancy; through maternity, at delivery; or through the MCH department, at their first postnatal infant visit. Women must be at least 18 years of age and their HIV-exposed infant less than 24 weeks of age to be eligible for the study. Pregnant women/mothers will be informed by trained research or clinical staff of the purpose of the research, the potential benefits, and the risks. They will also be counseled on expectations for POC testing at the time of delivery or within 2 weeks if delivery does not occur in the hospital, and the importance of returning for the birth PCR results and retesting at 6 weeks. Those agreeing to participate will provide written informed consent prior to enrollment in the study (Additional file 1). Clinical staff will promote participant retention and complete follow-up by continued outreach to enrolled mothers at ANC and MCH appointments. Infants of mothers who decline participation in the study will receive the on-site standard of care (SOC) EID (laboratory-based HIV DNA PCR testing at 6 weeks). The study protocol complies with the Helsinki Declaration and was reviewed and approved by the Institutional Review Boards at the Kenya Medical Research Institute (protocol KEMRI/SERU/CVR/018/3390) and the University of Kansas Medical Center (protocol # 00140399). A data monitoring committee was not required because the interventions are minimally invasive diagnostic strategies posing no elevated risks of severe outcomes. Protocol modifications will be communicated to facility personnel by research team site coordinators.

#### Pilot POC intervention

##### Personnel training

Study staff will be trained in procedures for informed consent and study enrollment and the protection of patient confidentiality. The hospital maternity staff will be trained to conduct a heel stick and collect two samples at each time point (DBS and whole blood). A half-day of training will be provided to EID staff on the equipment, cartridges, and procedures used to conduct POC tests at their hospital. Study coordinators at each site will arrange periodic refresher training and new personnel training as rotation of staff occurs.

##### Birth testing

For all infants presenting for birth testing (within 2 weeks of age), the designated staff at each facility will collect two blood samples. A whole blood sample for POC testing (Xpert HIV-1 Qual or Alere q HIV-1/2 Detect) will be processed on-site by healthcare providers using test cartridges and POC machine. POC test results will be recorded in study logs and printout results from each of the POC machines will be attached to the infant’s clinical file (see *Data collection*, below). Mothers will be notified of the POC test result on the same day as testing or before infant’s hospital discharge (within 24 h). The second sample will follow the established SOC procedures for HIV DNA PCR testing: a dried blood spot (DBS) sample will be sent by courier to the hospital’s designated central laboratory for standard HIV DNA PCR. Results of HIV DNA PCR processed in the central laboratory will be recorded on paper forms and returned to the hospital by courier service. When the HIV DNA PCR result is received at the hospital, the mother will be called to return for result notification and counseling. If the infant has an HIV-positive test result (by either POC or PCR), the mother and infant will be linked to the Comprehensive Care Center (CCC) for same-day ART initiation. HIV-positive infants identified through this study will receive additional clinical monitoring (ART adherence, viral suppression, and immune system strength) through 24 months of age. HIV-negative infants will be scheduled to return to the hospital for six-week postnatal appointments and repeat HIV testing (HIV DNA PCR and POC).

##### Six-week testing

All infants who present for care at 4 to < 24 weeks of age, not previously diagnosed HIV-positive, will be eligible for 6-week testing. The same sequence of DBS and whole blood sample collection, DBS shipment for processing off-site, POC processing in clinic, result notification, and ART initiation (for HIV-positive infants) will be conducted as at birth. The optimal test sequence of an HIV-negative infant will be complete when HIV results at birth and 6 weeks postnatal have been provided to mothers.

##### Discordant results

In the case of discordant POC/HIV DNA PCR test results at birth or at 6-weeks, the infant will be initiated on ART based on the positive result from either method. A second, confirmatory sample will be collected and processed using both the POC and HIV DNA PCR procedures. A third sample will also be sent to the national reference lab for HIV DNA PCR processing. The infant will continue on ART until the results of the HIV DNA PCR test and the National Reference Lab results are available. ART continuation will be based on the HIV DNA PCR results.

##### ART adherence monitoring of HIV-positive infants

In order to monitor ART adherence and viral suppression, we will order quarterly CD4 and viral load (VL) tests for all HIV-positive infants until 24 months of age. At each time point, mothers of HIV-positive infants will take a brief survey, administered by the pediatric ART provider, regarding ART adherence and side effects. Since we anticipate that infants will be started on ART significantly earlier than in SOC, this increased monitoring is intended to characterize infants’ virologic and immunologic responses to early treatment, providing preliminary data to inform design of a larger-scale randomized trial.

##### Data collection

Using Epi Info software (US Centers for Disease Control and Prevention), site coordinators will collect and maintain a comprehensive electronic record of each infant’s relevant clinical data including date of birth, location of birth, POC sample collection and processing dates, POC test results, POC result notification to mothers, dates of SOC sample collection and return of results to the hospital, results of HIV DNA PCR test, mother notification of HIV DNA PCR results, and date of initiation of HIV-positive infants on ART. To ensure complete and accurate clinical data entry, site coordinators will periodically cross-check Epi Info files with various clinical records including ANC registers, maternity records, HIV-exposed infant registers, mother and infant clinical files, and hard copies of laboratory diagnostic results. Data pertaining specifically to treatment of HIV-positive infants (including ART initiation, OI prophylaxis, and viral load and CD4 monitoring through 24 months) will be accessed from HIV exposed infant registers, CCC records, and infant clinical files.

Study-specific data collection logs will track enrollment across varying departments, reasons for enrollment refusal, use of the POC machines including dates and times of sample collection and processing and the personnel processing the test, POC machine errors and their effect on clinical care, adverse events that occur as a result of the study, communication between clinical or study staff and participants, and hospital or national-level events that may impact clinical care and study operations. These logs will help gauge implementation feasibility and provider experience. The principle investigator and IRB-certified research staff will have access to the final trial dataset, with no contractual hindrances.

##### Experience of providers

Qualitative data will be collected on providers’ implementation experience. The study site coordinator at each hospital will conduct monthly meetings including department heads (PMTCT, Maternity, MCH, Laboratory, Outpatient Department, and CCC) and all providers engaged in study implementation. While meeting guides were developed using the Consolidated Framework for Implementation Research (CFIR) as a guide [32], questions will vary to ensure responsiveness to provider concerns and challenges expressed at different stages of the study. Topics of these discussions will include training and sensitization of personnel; stakeholder coordination; sensitization, enrollment, and satisfaction of mothers; deployment of POC testing; workflow optimization; management of the test cartridge supply stream; technical challenges; and context-specific solutions. The study team will review themes after each meeting to inform any required modifications to POC implementation (phase 2). Participants will complete an informed consent at the first meeting for permission to audio record the sessions for later transcription and analysis of the implementation experiences at each hospital.

##### Calculating costs of POC

Costs associated with each POC strategy will be collected and compared to the existing EID testing process. We will estimate costs from a donor or government perspective to calculate and compute costs of integrating each POC strategy into an existing system compared to HIV DNA PCR processed at central laboratories, the current gold standard for EID care. We will use standard procedures for intervention cost estimation [33].

#### Fidelity assurance procedures

Standard operating procedures (SOPs) were developed to standardize training, enrollment, and data collection. Personnel will be trained on the SOPs, which will be kept available at each site for convenient reference. Study management will provide supportive supervision visits quarterly to assess protocol adherence. The objectives of these visits include overseeing and assisting with formative interviews with key stakeholders, providing site-level training on study protocols to clinical and study staff, review of consent forms, and discussion of any challenges with the study team. Technical competence and compliance with POC SOPs will be evaluated by a checklist that includes maintenance of workspace, blood collection technique, operation of the machine, cartridge-loading technique, following machine prompts through to result reporting and archiving, biosafety and waste disposal procedures, and test documentation. Furthermore, the study team will hold a bi-weekly study call to update enrollment numbers, review study logs, and address any challenges or concerns with the consent process or study implementation. Site coordinators are required to report any adverse event immediately to the US- and Kenya-based principle investigators. Adverse events would include unintentional disclosure of HIV status or emotional distress related to study participation. Infant death is a non-study-related adverse event also reported to the IRB.

Performance and reliability of the POC tests will be monitored by sending every tenth specimen to the national reference laboratory for confirmatory testing by HIV DNA PCR. By agreement with the national POC technical working group, each infant sample with an HIV-positive POC or HIV DNA PCR test result will be followed up by collection of a second sample for confirmatory testing at the national reference laboratory.

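### Every infant death is classed in advance as unrelated to the study, although study test results start, and in discordant cases can end, infant antiretroviral therapy (ART)

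*Protocol article*

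**What the plan says.** Fidelity assurance procedures gives the reporting rule. Site coordinators report any adverse event immediately to the principal investigators. The examples given are non-clinical: "Adverse events would include unintentional disclosure of HIV status or emotional distress related to study participation". The next sentence reads: "Infant death is a non-study-related adverse event also reported to the IRB". The section describes no assessment of individual deaths.

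Elsewhere the article describes what a study result does to an infant's care:

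- **Birth testing:** after a positive result by POC or PCR, mother and infant are "linked to the Comprehensive Care Center (CCC) for same-day ART initiation". Six-week testing follows the same sequence.
- **Discordant results:** "the infant will be initiated on ART based on the positive result from either method". After repeat and reference-laboratory testing, "ART continuation will be based on the HIV DNA PCR results".
- **Data collection:** the study logs include "adverse events that occur as a result of the study".

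**The concern.** Whether a death is related to study procedures is a judgement made on the facts of the case. The sentence makes that judgement for all infant deaths at once, as part of the definition. If a death did follow from a study result, or from treatment started or stopped on one, the rule as worded would still call it unrelated.

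At stake is the safety reading of the pilot. The article says that its results will go to a national technical working group and the Ministry of Health. A statement that no infant death was study-related would carry no information if the classification could not have come out otherwise.

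**Working it through.** No arithmetic decides this point. The check is whether the article describes routes by which study participation could bear on an infant's survival. If it does, relatedness cannot be ruled out in advance.

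**Step 1. What the study adds.** Under Participant recruitment, eligibility, and consent, infants of mothers who decline have laboratory PCR at 6 weeks. The birth test and both POC tests therefore come with participation. Under ART adherence monitoring, the protocol expects ART to start markedly earlier than under standard care, and it surveys side effects in HIV-positive infants.

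**Step 2. Routes from a study result to a clinical consequence.**

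| Route | Where the article describes it | What limits it |
|---|---|---|
| Earlier ART after a positive study test, with possible side effects | Birth testing; Discordant results; ART adherence monitoring | Side effects are surveyed quarterly to 24 months |
| ART started on a false positive | Birth testing; Discordant results | Second sample to the reference laboratory after every positive (Fidelity assurance procedures); cited POC specificity of 100%, similar in field studies (Background) |
| ART ended on a false-negative PCR after a true-positive POC result | Discordant results | Discordant cases only; repeat POC and PCR plus a reference-laboratory PCR come first |
| Missed 6-week retest after a negative birth result | Discussion | Retest rates are a planned measure (Table 1) |

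**Step 3. How likely a wrong result is.** The Background cites DNA PCR sensitivity of 68% at birth and 88% at 4 weeks. One test would then miss 100% − 68% = 32% of infected infants at birth and 100% − 88% = 12% at 4 weeks. These are single-test figures. They cannot be carried through the repeat and reference-laboratory sequence for discordant results, because the article gives no error rate for that sequence. They do show that a falsely negative birth result is foreseeable.

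**Step 4. Size.** Planned enrolment is 15 per site per month × 4 sites × 12 months = 720 mother-infant pairs, which matches the article. The article gives no infant mortality rate, and it says the expected number of HIV-positive infants is too small for robust sensitivity or specificity. The number of deaths that could be related to a study result is therefore unknown, and zero is plausible.

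**Step 5. Comparison.** The article's case for birth testing is that the timing of diagnosis affects early mortality. It also names a way in which birth testing might reduce later detection. A rule that no infant death can be related to the study does not agree with either statement.

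**The case against.** The strongest reply is that the sentence is loosely worded and little follows from it. Several parts of that reply stand:

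- Deaths are not hidden. The article classes infant death as an adverse event, so it goes to the principal investigators at once, and it also goes to the IRB. Nothing stops either from disagreeing with the label.
- The false-positive route is unlikely on the article's own figures, because every positive is followed by reference-laboratory confirmation.
- PCR decides continuation only where results are discordant, and after repeat testing.
- Study-related death is neither an objective nor an outcome in Table 1, so no planned estimate changes.
- Detailed causality procedures may sit in the full protocol or the standard operating procedures, which are not shown.

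The last point would answer a complaint that detail is missing. It does not answer this one, because the article states a rule, and the rule prejudges the answer.

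A reader might infer two stronger claims that the documents do not support. The first is that deaths are excluded from the study logs. Data collection lists "adverse events that occur as a result of the study" among the log contents, but it does not say that other events are left out. The second is that the decision to have no data monitoring committee depends on the label. The reason given is that "the interventions are minimally invasive diagnostic strategies posing no elevated risks of severe outcomes", and that statement neither cites the classification of deaths nor needs it.

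**Conclusion.** The concern holds in a limited form. The article fixes the relatedness of every infant death in advance, and that does not fit its own account of how study results change treatment and may change retesting. The defect is the label, which as worded leaves no place for a case-by-case judgement. It is not a failure to capture or report deaths.

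The size cannot be estimated from the documents and may be zero. The conclusion does not assume that any death will be caused by the study. It rests on reading the sentence as applying to all infant deaths, and the sentence states no exception. It would be wrong to read the point as evidence of harm.

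**What to change.** In Fidelity assurance procedures, delete the qualifier *non-study-related* and keep the reporting of infant deaths to the IRB. Add that the investigators judge the relatedness of each infant death, using the POC and PCR results and the ART dates. Enter every infant death in the study log, whatever its relatedness.

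The test results and the date of ART initiation are already listed under Data collection. A date of stopping ART is not listed, but infant clinical files are a named data source and can be checked. Enrolment was still open when the article was written, so deaths already reported can be reviewed in the same way.

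The cost is one edited sentence, one added sentence and a short review per death. No new outcome or analysis is needed, and no testing or treatment rule changes.
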